## AIM

### A. SPECIFIC AIMS

Our sample will consist of 370 families with a high school senior, half of whom will be assigned randomly to a prevention group (SAAF—EAP) and half of whom will be assigned to a control group. Pre-intervention, post-intervention, and follow-up assessments of youths' substance use and secondary outcomes will be conducted with the entire sample. Our specific aims are as follows:

1. To test the hypothesis that rural African American emerging adults randomly assigned to participate in SAAF—EAP, compared to control participants, will demonstrate lower rates of substance use initiation, and that those who already use substances (e.g., cigarettes; alcohol, including binge drinking; marijuana and other illicit substances) will use them less frequently and consume lower quantities, at each follow-up assessment.
2. To test the hypothesis that SAAF—EAP primary caregivers and emerging adults, compared to control participants, will report higher levels of autonomy-promoting parenting and responsiveness in family relationships at each follow-up assessment.

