### D. RESEARCH METHODS

#### D1. Participants

A random sample of 370 rural African American families with a son or daughter in the last semester of public high school from each of 6 counties in central Georgia will participate in the study.

*D1.1. Random Assignment, Other Programs, and Contamination:* Families will be assigned randomly to either the prevention or control condition.

*D1.2. Inclusion/Exclusion criteria:* We will recruit all youth from public schools in their senior year of high school in the target counties that self-report being African American or Black and age 17-19. We will exclude from the pool of potential participants a small number of students whose participation in the intervention's group-based activities may create negative iatrogenic effects (Dishion, McCord, & Poulin, 1999). Students who have been suspended from school more than once and those who were expelled from a high school other than the one they are attending will be disqualified.

*D1.3. Family Recruitment and Retention Strategies:* The recruitment process will be carried out in the following sequence: (1) a letter will be mailed to parents/guardians from the school principal informing them of the study, (2) a home visit will be made by a community liaison to obtain active consent from primary caregiver and student to implement the screening procedures described previously, and (3) families will be invited to participate with active consent obtained from primary caregivers and active assent from emerging adults.

*D1.3a. Principals' letter:* Each primary caregiver of an African American high school senior who is selected randomly from the pool of potential participants will receive a letter from the school principal describing the study and the collaboration with the University of Georgia (UGA). Caregivers will be informed that they will be contacted by representatives associated with UGA (community liaisons) and they and their high school seniors may be invited to participate.

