**D6.3. *Power Analysis:*** As mentioned in Section D1, 690 families will be recruited to allow for an attrition rate of 15%. Power analyses were based on an effect size of .30 (Durlak & Wells, in press). Table 9.4.1 in Cohen (1977) can be used to calculate a necessary sample size of around 150 families per group to detect differences between the prevention and comparison groups with an alpha of .01 and a power of .90 for the dependent measures. For the analyses presented below using structural equation modeling (SEM), we considered both sample size and statistical power issues. The literature on sample size for latent variable structural equation analysis suggests that 150 cases are enough to ensure a reliable estimation of the model (see discussion by Tanaka, 1987). Much of this literature, however, is based on Monte Carlo studies of factor analysis models involving relatively few parameters (e.g., Boomsma, 1982). An alternate perspective is to consider the available sample size relative to the number of parameters that the model is estimating. For example, Bentler (1985) recommends at least 5 cases per parameter. We expect to have a sufficiently large sample to permit testing of the causal models described below. Based on the parameters derived from the research described in Section C, we conducted power analyses using Jöreskog and Sörbom's (1993) LISPOWER program. Our analyses evaluated the model's ability to detect the statistical significance of path coefficients that vary in their "true" magnitude, holding the other parameters in the model constant at values derived from the analyses presented in Section C. These power calculations were significantly different from 0 at  $p < .05$ . We evaluated the statistical power of these models for samples that varied in size from 150 to 170 cases. For the causal paths included in the models discussed in Section C, the power was above .80 for detecting path coefficients of .17 to .20 in absolute magnitude for samples of 150 cases or more. These coefficients correspond to those that Cohen (1988) termed small effects. These results suggest that we will have sufficient power to detect even relatively weak relations among variables.

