#### **D6.4 *Testing Hypotheses and Theoretical Models:***

**D6.4a *Latent growth modeling (LGM):*** Intervention researchers have begun to examine models that can detect differences between individuals in longitudinal rates of behavioral change. We will, therefore, use growth curve modeling to analyze our data, as they will allow us to examine predictors of change within, as well as across, individuals over time. In addition to standard linear models of growth, a variety of non-linear models (e.g., quadratic, logarithmic, non-parametric) will also be tested. Assumptions of homoscedasticity of residuals will be tested explicitly. After careful examination of the missingness mechanism (Schafer, 1997; Schafer & Graham, 2002), software that can accommodate missing data, such as HLM, AMOS, LISREL, or Mplus, will be used to estimate model parameters. This growth curve model allows for differences between individuals in rates of change over time. Because we are interested primarily in assessing differences at follow-up, the intercept will be centered around post-test or follow-up depending on the specific hypothesis being tested. Based on Muthén and Curran's (1997) results, our power to detect effects sizes of .2 or greater with an alpha of .05 is expected to exceed .8 with this sample size and a relatively balanced design. Estimates with ANCOVA also suggest power to detect significant differences at this level (Rausch, Maxwell, & Kelley, 2003).

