Several important issues must be considered that, due to space limitations, cannot be addressed in detail. First, research on LGM with substance use suggests that an S-shaped logistic function may be more appropriate than a linear function (see McArdle, 2002; Spoth, Redmond, Shin, & Azevedo, 2004). Second, as in any intervention study, the missing data mechanism must be integrated into the analytic plan while considering patterns commonly observed in a mixture model. For example, the groups may include participants engaging in low levels of substance use at the beginning of the study who do not increase their use, early initiators who maintain their initial use levels, participants who increase use gradually, and so forth. We will address this issue by integrating the missing data mechanism (e.g., Hedeker & Gibbons, 1997) and the various types of trajectories (e.g., Muthén, 1997; Nagin & Tremblay, 2001) into a single integrated analytic framework. In addition to this approach, we will also estimate random effects Tobit models using Stata. This allows for the censoring of substance use at 0. Nonusers may vary in the strength of their avoidance of usage; some may be seriously considering trying a particular substance whereas others have no intention whatsoever of using. We will evaluate these models in comparison with others appropriate for our outcome measures, including zero-inflated Poisson and negative binomial models (Long, 2003).

*D6.4b. Aim 5: Testing mediational paths in the causative model:* With our proposed sample size and design, we should be able to detect an effect size of .20 or greater 80% of the time with an alpha of .05 (Muthén & Curran, 1997). The sample is larger than needed for detection of significant group differences because we also plan to contribute to theory development by testing mediational pathways; proposing a framework for exploratory analyses; examining moderators of change; comparing various developmental trajectories; and identifying all relevant individual, intervention-related, and time-varying covariates in our analyses.

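### AIM's power section plans on 690 families, but its D1 and Specific Aims recruit 370; at 370 the claim of over 80% power for an effect of .2 is unsupported

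*Combined protocol and SAP*

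**What the plan says.** All references are to the AIM protocol, the second of the two in the combined document.

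- **Specific Aims (A):** "Our sample will consist of 370 families with a high school senior", "half of whom will be assigned randomly to a prevention group" and the other half to control.
- **D1 Participants:** "A random sample of 370 rural African American families with a son or daughter in the last semester of public high school" will take part.
- **D6.3 Power Analysis:** "As mentioned in Section D1, 690 families will be recruited to allow for an attrition rate of 15" per cent. The same section then derives a need of around 150 families per group, for an effect size of .30 at alpha .01 and power .90.
- **D6.4a, latent growth modeling:** "our power to detect effects sizes of .2 or greater with an alpha of .05 is expected to exceed .8 with this sample size". It adds, by citation, that ANCOVA estimates point the same way.
- **D6.4b, mediational paths:** with the proposed sample size, "we should be able to detect an effect size of .20 or greater 80% of the time with an alpha of .05". It describes the sample as larger than group comparisons require.

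Neither D6.4a nor D6.4b says whether the sample size meant is 690 or 370. No pretest–outcome correlation, sidedness or definition of the .2 effect is given.

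**The concern.** D6.3 cites D1 for a number that D1 does not contain, and the number D1 does contain is little more than half as large. The analysis section's only recruitment figure is 690, so a reader of D6.4 will naturally take that as the sample in question. If 370 families are recruited, the statements that effects of .2 can be detected with 80% power may describe a study about twice the size of the one being run.

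The practical risk lies in interpretation. A null result read against D6.4a would suggest that effects of .2 had been sought with at least 80% power. At 370 that holds only under a strong correlation that the plan never states.

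**Working it through.** **Inputs from the documents.** Recruitment 690 (D6.3) or 370 (A, D1); equal allocation (A); attrition 15% (D6.3); effect .2, alpha .05, power above .8 (D6.4a).

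**Assumptions, because the documents are silent.** The effect .2 is a standardized mean difference *d*; the test is two-sided; the pretest–outcome correlation ρ is varied.

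**Step 1. Retained families per arm.**
- 690 × 0.85 / 2 = 293.25
- 370 × 0.85 / 2 = 157.25 (185 per arm with no loss)
- Ratio 690 / 370 = 1.86

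**Step 2. Try to reproduce the claim of power above .8.** With *n* per arm, power = Φ( *d* / √(2(1 − ρ²)/*n*) − 1.96 ). Setting ρ = 0 gives the unadjusted comparison.

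Example at *n* = 157.25, ρ = .6: √(2 × 0.64 / 157.25) = 0.0902; 0.2 / 0.0902 = 2.217; Φ(0.257) = .601.

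| *n* per arm | ρ = 0 | ρ = .5 | ρ = .6 | ρ = .7 |
|---|---|---|---|---|
| 157 (370, 15% loss) | 43% | 53% | 60% | 70% |
| 185 (370, no loss) | 49% | 60% | 67% | 77% |
| 293 (690, 15% loss) | 68% | 80% | 86% | 92% |

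The claim is not reproduced at 370 anywhere in this range. At 690 after loss it is reached, to rounding, from ρ = .5 upward.

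**Step 3. Correlation needed for 80%.** The unadjusted requirement is 2 × (2.80 / 0.2)² ≈ 392 per arm, so ρ = √(1 − *n* / 392).
- 157 per arm: about .77
- 185 per arm: about .73
- 293 per arm: about .50

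**Step 4. Growth model.** D6.4a's claim is mainly about a growth model, so I also took three visits at 0, 4.5 and 13.5 months (6-week programme, posttest 3 months later, follow-up 9 months after that). I assumed a linear slope, a common correlation of .6 between visits and a difference of .2 at the last visit. Generalized least squares gives 52% power at 157 per arm with free pretest means and 60% with a common pretest mean. At 293 per arm the figures are 79% and 86%. The pattern matches ANCOVA.

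**Step 5. Effect detectable with 80% power at 157 per arm.** 2.80 × √(2 / 157.25) = .316, multiplied by √(1 − ρ²):
- ρ = 0: .32
- ρ = .5: .27
- ρ = .6: .25
- ρ = .7: .23

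**Step 6. If .20 in D6.4b is a correlation or path coefficient.** By Fisher's z with 314.5 families in total: Φ(0.2027 × √311.5 − 1.96) = Φ(1.62) ≈ .95. On that reading the claim holds comfortably at 370.

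**The case against.** **690 may be a stray number.** The rest of D6.3 fits 370: two groups of 150 inflated for 15% loss need 300 / 0.85 = 353 families, and 370 retains 157 per group. Nothing explicitly ties D6.4 to 690. This stands, so it cannot be said that the power claims were computed at 690. Against it, D6.4b calls the sample larger than group comparisons need, which suits 293 per arm (nearly twice 150) better than 157 (5% above it). Either way the text must be reconciled.

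**D1 mentions each of 6 counties.** Reading 370 as a per-county figure contradicts the Aims and still does not give 690.

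**157 per arm is a worst case.** D6.1 plans full-information maximum likelihood and multiple imputation, so partly observed families contribute. This is fair, and it is why the no-loss row is shown. At 185 per arm, 80% still needs a correlation of about .73.

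**The cited power sources may contain the missing assumptions.** They may, but the plan does not state them and they cannot be checked from the documents.

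**A reader might infer that the power claim is simply false.** The documents do not support that. It would be true at 370 with a correlation near .77 after loss. Nor does the 690/370 conflict decide it alone: an unadjusted two-sided test misses 80% at 690 too (75%, or 68% after loss).

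**A reader might also infer that a true effect of .2 would more likely be missed than found.** Only the unadjusted figures, 43% and 49%, say so. D6.4a plans growth models and ANCOVA, and the adjusted figures calculated here all exceed 50%.

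**Conclusion.** The contradiction is certain: D6.3 gives 690 and attributes it to D1, while D1 and the Aims give 370. It changes the retained sample from about 293 to about 157 per arm.

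The consequence for power is conditional. If .2 in D6.4a is a standardized mean difference tested two-sided at .05, power above .8 is unsupported at 370. It is 53% to 70% by ANCOVA after loss for correlations of .5 to .7, and 60% to 77% with no loss. At 690 after loss the same correlations give 80% to 92%. The mean-difference reading suits D6.4a, which appeals to ANCOVA and a balanced design. It is less secure in D6.4b, whose subject is mediation; there the metric has to be stated before the claim can be judged.

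This must be fixed, because the power statements cannot be interpreted until the sample size is settled.

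**What to change.** 1. State one recruitment target and the retained number in A, D1 and D6.3. If A and D1 are right, that is 370 recruited and about 157 per arm after 15% loss. Correct the cross-reference in D6.3.
2. In D6.4a, replace the power statement with the effect detectable at that number, giving the metric, sidedness and assumed pretest correlation. For 157 per arm, two-sided .05 and 80% power: *d* of about .32 at correlation 0, .27 at .5, .25 at .6 and .23 at .7.
3. In D6.4b, say whether .20 is a mean difference or a path coefficient, and restate the power accordingly.

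If 370 is the intended target, the cost is wording only, with no added enrolment. The one downside is a less favourable stated detectable effect.

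### AIM D6.3: the figure of about 150 families per group cannot be reproduced from an effect size of .30, alpha .01 and power .90

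*Combined protocol and SAP*

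**What the plan says.** AIM section D6.3 states: "Power analyses were based on an effect size of .30". Its requirement, which it takes from a cited table, is "a necessary sample size of around 150 families per group to detect differences between the prevention and comparison groups with an alpha of .01"; the target power is .90. It gives no formula, metric for the .30, sidedness or covariate adjustment.

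The number to be recruited appears twice, with different values. D6.3 gives 690 families, allowing for 15% attrition, and refers back to D1. The Specific Aims and D1 give 370, and the aims split them half and half between the arms.

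D6.4a adds growth-model power for effects of .2 at alpha .05, and mentions ANCOVA without giving a pretest-outcome correlation. D6.4b repeats the .20 claim and then says: "The sample is larger than needed for detection of significant group differences".

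**The concern.** A standardised difference of .30 is modest, while alpha .01 with power .90 is a demanding pair of criteria. A requirement of 150 per group looks far too small for that combination. SAAF-T, the companion protocol in the same file, says that 250 per condition detects an effect of .25 with 80% power at the .05 level. It would be surprising if AIM needed only 150 per group for .30 at a stricter alpha and higher power.

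This sentence is the only derivation of a sample size for AIM's two-group comparison. If it is wrong, readers will take a null result as stronger evidence than it is, and the number recruited has no reproducible basis on this criterion.

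**Working it through.** **Inputs.** Effect size .30, alpha .01, power .90 and 150 per group come from D6.3. Equal allocation comes from the Specific Aims. The 15% attrition and 690 families come from D6.3, and 370 from the aims and D1. Metric, sidedness and adjustment are not given, so each is varied below.

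**1. Standardised mean difference d = .30, unadjusted.** n per group = 2(z_alpha + z_power)² / d².
- Two-sided: 2(2.5758 + 1.2816)² / .09 = 330.7, so 331 per group (333 by noncentral t).
- One-sided: 2(2.3263 + 1.2816)² / .09 = 289.3, so 290 per group.
- Allowing for attrition, two-sided: 331 / 0.85 = 389.4, so 390 per group recruited.

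Power at 150 per group = Φ(.30 × √(150/2) − z_alpha).
- Two-sided: Φ(2.598 − 2.576) = .509 (.503 by noncentral t).
- One-sided: Φ(2.598 − 2.326) = .607.

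**2. Could adjustment explain 150?** The difference detectable with 150 per group at .01/.90 is 3.8574 × √(2/150) = .445. Bringing the requirement for .30 down to 150 needs a pretest-outcome correlation of √(1 − 150/330.65) = .74. No correlation is stated anywhere in AIM.

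**3. Other metrics** (noncentral F, 1 numerator df, λ = f² × total N, alpha .01, power .90):

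| Reading of .30 | f² | Total needed | Per group | Power with 150 per group | Implied d |
|---|---|---|---|---|---|
| f | .09 | 169 | about 85 | 99.5% | 2 × .30 = .60 |
| r | .09/.91 = .099 | 154 (158 by Fisher z) | 77 | 99.8% | 2 × .30/√.91 = .63 |
| f² | .30 | 54 | 27 | above 99.9% | not computed |

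None gives 150 per group. The nearest match is r = .30, where 150 families in total give 89.1% power.

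**4. Which metric is likely?** The SAAF-T figure reproduces as a mean difference: Φ(.25 × √125 − 1.960) = Φ(.835) = .798. That supports reading .30 as d, but it comes from a different trial's section and does not settle the matter.

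**5. Power of the planned sample for d = .30, unadjusted.** 370 × 0.85 / 2 = 157.25 per group; 690 × 0.85 / 2 = 293.25 per group.

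| Recruited | Per group | .01 two-sided | .01 one-sided | .05 two-sided |
|---|---|---|---|---|
| 370 | about 157 | 53% | 63% | 76% |
| 690 | about 293 | 85% | 90% | 95% |

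**6. With pretest adjustment (assumed correlations).** Dividing the standard error by 1/√(1 − ρ²), that is, multiplying it by √(1 − ρ²), 157 per group with ρ = .5 to .6 gives 69–77% at alpha .01 and 87–91% at alpha .05, two-sided.

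**The case against.** The strongest reply is that the plan never says .30 is a mean difference. If it is f or r, 150 per group gives more than 99% power and the stated number is generous. A reader might infer from the 51% that AIM lacks its stated power. The documents do not support that as an unconditional statement: it needs the mean-difference reading and it depends on which recruitment total is right. With 690 families, a one-sided test reaches about 90%, and Aim 1 is directional, although no one-sided test is declared. An assumed pretest correlation of .5 would bring two-sided power with 690 to about 95%.

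This limits the conclusion but does not rescue the sentence. On the f and r readings the necessary number is about 85 or 77 per group, so 150 per group is still not what the inputs give.

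Two further inferences go too far. One is that the remark in D6.4b about the sample being larger than needed rests on the 150. D6.4b does not cite that figure, and the remark directly follows a growth-model claim. The other is that the figure clashes with the .2 effects in D6.4. Those belong to repeated-measures models at alpha .05 and power .80, with the metric again unstated, so no contradiction is shown.

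It is also fair that D6.3 and D6.4 offer separate support through path-coefficient and growth-model power, which this check does not test.

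**Conclusion.** The figure of about 150 per group is wrong or incompletely specified as written. As a mean difference, two-sided and unadjusted, the stated criteria need 331 per group, and 150 gives about 51% power; one-sided, the figures are 290 and 61%. As r or f, the requirement is about 154 or 169 in total, for a mean difference of about .60 to .63, twice the size the sentence suggests. Only an unstated adjustment with a correlation near .74 would bring a mean difference of .30 to 150 per group.

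The failure to reproduce does not depend on choosing a metric; the size of any shortfall does. The mean-difference reading is the natural one, but it remains an assumption. The table the plan cites is not in the documents and was not used. The sentence needs correcting because no other derivation of the number per group is given for AIM's group comparison.

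**What to change.** 1. In D6.3, state the metric of the .30, the sidedness of the test and any covariate adjustment.
2. Reconcile the 690 families in D6.3 with the 370 in the Specific Aims and D1.
3. Replace the sentence with the power the reconciled sample delivers. If .30 is a mean difference, two-sided and unadjusted, the figures after 15% attrition are 53% at alpha .01 and 76% at alpha .05 for 370 recruited, or 85% and 95% for 690. If .30 is r or f, correct 'per group' to a total and give the equivalent mean difference.
4. Label any pretest-adjusted figure as resting on an assumed correlation and show a range, such as the one for .5 to .6 above.
5. Keep the D6.4b remark on sample size only if the restated figures support it.

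The cost is a short rewrite. Stated power will look less favourable on the mean-difference reading. The correction itself requires no more families.

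### AIM's mediation aim carries an 80% power claim for an effect of .20 and a single-path power figure, but neither is power for an indirect effect, and with 370 families the 80% is reached only under strong pretest adjustment

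*Combined protocol and SAP*

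**What the plan says.** All references are to the AIM part of the combined document.

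- **D6.3, group comparison.** "Power analyses were based on an effect size of .30". The section derives "a necessary sample size of around 150 families per group to detect differences between the prevention and comparison groups with an alpha of .01" and power .90.
- **D6.3, structural models.** "We expect to have a sufficiently large sample to permit testing of the causal models described below". The support offered is a power run for individual paths in the models of Section C, for "samples that varied in size from 150 to 170 cases", "holding the other parameters in the model constant at values derived from the analyses presented in Section C". The result is that "the power was above .80 for detecting path coefficients of .17 to .20 in absolute magnitude for samples of 150 cases or more", at the .05 level. The section concludes that even fairly weak relations will be detectable.
- **D6.4b (Aim 5, mediational paths).** It states that an effect size of .20 or more should be detected 80% of the time at alpha .05, citing the growth-model source also used in D6.4a. It adds: "The sample is larger than needed for detection of significant group differences because we also plan to contribute to theory development by testing mediational pathways".
- **Sample size.** A. Specific Aims and D1 give 370 families, half per condition. D6.3 gives 690, attributes that number to D1, and allows for 15% attrition.

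The plan gives no power for an indirect effect, names no mediation test, and does not define the metric of the .30 or the .20 or the link to which each applies.

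**The concern.** In a mediation model of a randomised trial the first link starts at the two-level arm variable. The standardised path from a balanced arm is about half the standardised mean difference, so effects that look comfortably larger than .17–.20 fall below that range once put on the path scale. An indirect effect also requires both links to be found, so the power of one path can only be an upper limit on the power of the pair.

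Mediation is the stated reason for having more families than the group comparison needs. If its power is much lower than claimed, a null result under Aim 5 could be taken as evidence against the causal model when the test had little chance of supporting it.

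**Working it through.** **Inputs.** From the plan: effects .30 and .20; paths .17–.20; alpha .05; 150–170 cases; 370 or 690 families; 1:1 allocation; 15% attrition. Retained numbers are 370 × .85 = 314 (157 per arm) and 690 × .85 = 586 (293 per arm). Assumed: two-sided tests; effects are standardised mean differences between arms on the mediator; one mediator; mediator-to-outcome path b of .17–.20, borrowed from D6.3.

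**The plan's single-path figure.** Power = Φ(atanh(r)·√(N−3) − 1.96).
- N = 150: .55 (r = .17) and .69 (r = .20).
- N = 170: .60 and .75.
- N = 300, if 150 means per group: .84 and .94.
- N = 150 total also gives about .80 if other predictors explain roughly 20% (r = .20) to 45% (r = .17) of the variance.

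The figure can therefore be neither confirmed nor refuted without the Section C parameters.

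**Arm effect as a path.** r = d/√(d²+4).
- d = .30: .30/√4.09 = .148.
- d = .20: .20/√4.04 = .0995.
- In reverse, d = 2r/√(1−r²): r = .17–.20 corresponds to d = .35–.41, above both planning effects.

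**Arm link.** Power = Φ(d/[√(2/n)·√(1−ρ²)] − 1.96), where n is per arm and ρ is the pretest correlation. With n = 157, √(2/n) = .1129.
- d = .30: .30/.1129 = 2.66, power .76. With ρ = .6 (36% of variance): 3.32, power .91.
- d = .20: 1.77, power .43. With ρ = .6: 2.21, power .60.

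**Mediator link.** By the single-path formula, power at b = .17 and .20 is .857 and .947 (N = 314), .908 and .973 (N = 370), and .986 and .998 (N = 586).

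**Joint power** is the product of the two. For example, at 314 and d = .20: .43 × .857 to .43 × .947, about .36–.40.

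| N analysed | Effect | Arm link, unadjusted | Joint, unadjusted | Joint, pretest explains 36% |
|---|---|---|---|---|
| 314 | .30 | .76 | .65–.72 | .78–.91 |
| 314 | .20 | .43 | .36–.40 | .52–.60 |
| 370 (no loss) | .30 | .82 | .75–.80 | .86–.95 |
| 370 (no loss) | .20 | .49 | .44–.47 | .61–.67 |
| 586 | .30 | .95 | .94–.95 | .98 or more |
| 586 | .20 | .68 | .67–.68 | .84–.86 |

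In the last column the lower value adjusts only the mediator. The upper value also removes 36% of the outcome variance from the second link, where power = Φ(b·√((N−3)/(1−b²−.36)) − 1.96). At N = 314 and b = .20 that is .995, and .91 × .995 is about .91.

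Simulating the joint test at N = 314 without adjustment (4,000 runs per case) gave .66–.73 for .30 and .36–.39 for .20, in agreement with the product. The Sobel test was weaker: at b = .20, .55 and .23.

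**Pretest correlation needed for 80% on the arm link alone at d = .20.** ρ = √(1 − (.20/[2.802·√(2/n)])²).
- n = 157: √(1 − (.20/.316)²), about .78.
- n = 185: √(1 − (.20/.291)²), about .73.

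**The case against.** The strongest objection is the sample size. D6.3, the section that contains the path-power claim, says 690. At 586 retained, .30 is adequately powered without adjustment, and .20 passes 80% if pretest explains 36% of variance. A reader might infer that the mediation power is simply absent. The documents do not support that: it depends on which number is right. This stands, and it is why the conflict has to be settled first. The aims and D1 both give 370, so that case cannot be set aside.

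Second, neither effect is defined as arm-to-mediator. Combining d = .30 with b = .17–.20 implies an indirect path of only .148 × .17 to .148 × .20, or .025–.030 (d of about .05–.06). For d = .20 it is .017–.020 (d of about .03–.04). If .20 is instead the mediated effect itself, with equal links of √.0995 = .315, each link has power .977 at N = 150 and the joint power is .977², about .95. This also stands. It makes the low percentages conditional, and it shows that the 80% claim cannot be interpreted until the effect is defined.

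Third, full-information likelihood and multiple imputation are planned (D6.1b), so 314 complete cases is not the intended analysis set. That moves the answer at most to the 370 row, where .20 still falls short.

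Two further inferences are unsupported. The .17–.20 figure cannot be called wrong without Section C. Nor does the plan describe the arm path as a small effect: it applies that label to the Section C path coefficients. It also claims no power for moderators, so there is nothing to correct there.

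**Conclusion.** The concern holds in a limited form. AIM gives no power for an indirect effect, and its single-path figure does not cover arm paths of .148 and .0995. On the reading adopted here, the 80% claim for .20 in D6.4b fails at 370 families. Unadjusted joint power is .36–.47 between 314 and 370 analysed, and even the arm link alone needs a pretest correlation of about .73 to .78. For .30 at 370 families, power is moderate without adjustment and adequate in most cases with it. At 690 recruited, .30 is safe, and .20 depends on pretest adjustment.

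These figures rest on standardised mean differences applied to the arm-to-mediator link, two-sided .05, a single mediator, and b of .17–.20. The absence of any indirect-effect power does not depend on them.

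**What to change.** 1. Reconcile 370 (A. Specific Aims, D1) with 690 (D6.3), and state the number expected to be retained.
2. State the metric of the .20 and .30 effects and the link to which each applies.
3. In D6.4b, replace the 80% claim with power for the indirect effect at the retained number. Use a joint test of the two links, for .20 and .30, with the pretest mediator as covariate and its assumed correlation stated. In D6.3, stop using the single-path figure as support for the mediation tests.
4. If the number is 370, describe mediation at an effect of .20 as exploratory.

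The cost is restated text and some less favourable figures. Trial conduct does not change.
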